## Abstract

**Methods::**

This study is a randomized controlled trial involving 120 participants, and a total of 90 eligible RA patients will be randomly allocated to three groups in a 1:1:1 ratio as moxibustion at 7 to 9 am, moxibustion at 5 to 7 pm, and waiting list group, meanwhile, 30 healthy people will be divided into the control group. Patients in moxibustion groups will be treated for 30 minutes per session, 3 times a week, lasting 6 weeks. All of RA patients will be evaluated with questionnaires and laboratory tests before treatment, as well as 3 weeks, 6 weeks, and 3 months after treatment. One way analysis of variance (ANOVA) with multiple comparisons will be applied to identify differences more than two groups. Halberg cosiner software will be used to analysis the circadian rhythm.

**Results::**

The results of this study will be published in a peer-reviewed journal.

**Conclusion::**

This study will provide evidence-based evidence for the effective difference of Chrono-moxibustion in RA treatment and its influence on circadian rhythm of RA patients.

## 1. Introduction

Rheumatoid arthritis (RA) is a chronic autoimmune disease characterized by progressive and persistent synovitis. The main feature of its clinical manifestations possess circadian variation which shows light symptoms during the day and heavy symptoms at night.^[1]^ On the other hand, Previous findings suggested that the rhythm variations of clinical feature were attributed to the circadian oscillation of key inflammatory cytokines in RA. The Global Burden of Disease Study (2017)^[2]^ presented that the age-standardized prevalence and incidence rates of RA were increasing. RA affected 0.5% to 1.0% of the global population, seriously reduced life quality and damaged the physical and psychological health.^[3]^ Because of its complex etiology and pathology, protracted and difficult to recover, it has become one of the major difficult diseases concerned by all the medical field.

Currently, there are four main strategies of the approved RA treatment, including non-pharmacological treatments, non-steroidal antiinflammatory drugs (NSAIDs), disease-modifying antirheumatic drugs (DMARDs), and Glucocorticoids.^[4]^ While, there are also some recommended non-pharmacological treatments, such as physical therapy, functional exercise, patient counseling and complementary and alternative medicine.

NSAIDs can effectively relieve pain, swelling and improve joint function, while Glucocorticoids has rapid disease-modifying effects and DMARDs can ease symptoms and restrain the joint destruction clinically.^[5]^ Nevertheless, all of these currently available drugs showed severe side-effects and high cost.^[6]^ Hence, many RA patients are seeking complementary and alternative medicine such as acupuncture and moxibustion.

As a safe and effective therapy of traditional Chinese medicine (TCM), moxibustion has been widely adopted in the RA treatment for many years.^[7,8]^ Previous studies certified that moxibustion, which can significantly alleviate pain, swelling and stiffness, are effective in treating RA.^[9–11]^

In addition, chronotherapy has been developed in order to better fit circadian variations of clinical feature, improve efficacy and minimize adverse events (AEs). For instance, the modified-release prednisone was administered in the evening at 10.00 pm, which seemed more effective in ameliorating morning stiffness in RA patients.^[12]^

Acupuncture and moxibustion were performed according to time, which has been used clinically for thousands of years in China. As a consequence, the achievements of chronotherapy in Western medicine have prompted us to combine the RA pathological mechanism with Chrono-moxibustion which was conducted at different time. Our pilot study also suggested that Chrono-moxibustion can engender dissimilar therapeutic effects.^[13]^ Nevertheless, there is a lack of rigorous clinical randomized controlled trial to clarify dissimilar therapeutic effect of Chrono-moxibustion on RA. Besides, the clinical study of Chrono-moxibustion regulating the circadian rhythm of RA is relatively unavailable. Consequently, we will study the effectiveness of Chrono-moxibustion and explore its influence on circadian rhythm of RA patients.

## 2. Methods

### 2.1. Study design

The study aims to assess the effectiveness of moxibustion for RA, as well as to determine which time is more optimal in clinical practice. In addition, it will explore the influence of Chrono-moxibustion on circadian rhythm of RA patients. According to the validity of Chrono-moxibustion may adjust circadian rhythm of RA patients, we hypothesized there will be diverse effect by Chrono-moxibustion based on the theory of Chronobiology, moreover, it can also modulate the pathological rhythm of RA.

### 2.2. Study setting

A total of 90 RA patients will be divided randomly into 3 groups via a completely randomized digital table as moxibustion at 7 to 9 am (group A), moxibustion at 5 to 7 pm (group B) and waiting list group (group C) by a ratio of 1:1:1, meanwhile, 30 healthy people will be divided into control group (group D). This RCT will be conducted in multicenter with the assessor and statistician blinded to treatment allocation, and will be carried out at 4 hospitals in China: The Affiliated TCM Hospital of Southwest Medical University, the Luzhou Hospital of Traditional Chinese Medicine, Hejiang Hospital of Traditional Chinese Medicine and Rongchang District Hospital of Traditional Chinese Medicine. The specific process of participant inclusion is illustrated in Figure 1.

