### 2.4. Randomization and allocation concealment

Eligible patients will be randomly assigned to 3 groups in a 1:1:1 ratio. The computer-generated random number list will be concealed in sequentially numbered, opaque, and sealed envelopes which kept by an independent custodian to ensure allocation concealment. The patients’ screening sequence numbers will be printed on the outside while the group names will be printed inside the envelope. The practitioner will firstly verify each patient meet the eligibility criteria and sign the written informed consent form, and then open the sealed envelope which containing an allocation sequence number for each patient. If any error or disclosure regarding randomization occurs, a new randomization sequence will be generated starting from the problematic serial number and applied to subsequent patients from then on.

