### 2.9. Procedure

Potential participants will be initially screened according to the inclusion and exclusion criteria by our recruitment team, and those who may meet the eligibility requirements will be subjected to RA related serological testing for secondary evaluation. Eligible participants who are willing to take part in this trial will be asked to sign a written informed consent form after completing the screening tests. Then, all of eligible patients will be randomized to group A, group B, or group C. After randomization, subjects enter a 1-week baseline period then they will complete the baseline questionnaire and blood sampling at 4 equidistant time points within 24 hours. Subsequently, they will receive a 6-week moxibustion in the light of their group allocation and then provide blood specimens at 4 equidistant time points within 24 hours. After 3 weeks and 3 months, blood sample will be also collected. All the RA subjects will be evaluated with study-related scales before treatment, as well as 3 weeks, 6 weeks and 3 months after treatment. Three months after the end of treatment, all participants will be followed up to assess the curative effect and safety (Table 1).

**Table 1 T1:** The schedules for patient enrollment, interventions and assessments. SF-MPQ, short-form Mcgill pain questionnaire; DAS28, disease activity score of 28 joints.

Study schedule					
	Baseline	Treatment phase (Weeks 1–6)			Follow-up phase
Timepoint	Week –1	Week 0	Week 3	Week 6	Month 3
Patients					
Enrollment	√				
Informed consent	√				
Signed informed consent		√			
Medical history	√				
Physical examination	√				
Laboratory test	√				
Randomization		√			
Intervention					
Moxibustion at 7–9 am		√	√	√	
moxibustion at 5–7 pm		√	√	√	
Waiting list group					
Outcomes					
SF-MPQ	√		√	√	√
Laboratory indicators	√		√	√	√
Joints morning Stiffness score	√		√	√	√
Joints swelling index	√		√	√	√
Joints tenderness index	√		√	√	√
DAS28	√		√	√	√
Monitor					
Adverse events					√
Patient’s compliance					√
Reasons of drop-outs or withdrawals					√

DAS28 = disease activity score 28, SF-MPQ = Short-Form McGill Pain Questionnaire.

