### 2.12. Sample size calculation

The sample size has been estimated based on the results of a preceding study that had shown that moxibustion can ease RA patients.^[10]^ Results from a previous study showed that the mean changes in the Disease activity score in 28 joints (DAS 28) were 4.17 ± 0.94 (moxibustion group) and 4.86 ± 1.40 (control group). PASS software was used to calculate the sample size. The confidence of the trial sample size was 90% and the significance level was 0.05. Results showed that clinically significant differences would be detected using a minimum sample size of 26 individuals in each group. The maximum permissible withdrawal rate is 15% and 120 participants (30 per group) will be recruited.

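### As described, the allocation procedure secures neither 30 patients per arm nor balance of the arms within each of the four hospitals

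*Protocol article*

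**What the plan says.** - **Method and sites.** Section 2.2 has the 90 RA patients "divided randomly into 3 groups via a completely randomized digital table", and the trial "will be carried out at 4 hospitals in China". Section 2.4 adds: "Eligible patients will be randomly assigned to 3 groups in a 1:1:1 ratio".
- **Target numbers.** Section 2.12 gives a minimum of 26 per group, allows 15% withdrawal, and concludes that "120 participants (30 per group) will be recruited". One of those four groups is the healthy control group, which is not randomised.
- **Envelopes.** In section 2.4, "The computer-generated random number list will be concealed in sequentially numbered, opaque, and sealed envelopes". On these envelopes the patients' "screening sequence numbers will be printed on the outside while the group names will be printed inside the envelope". The practitioner opens the envelope after checking eligibility and obtaining consent.
- **Screening.** In section 2.9, "those who may meet the eligibility requirements will be subjected to RA related serological testing for secondary evaluation". This comes before randomisation, so some screened patients can fail.
- **Errors.** After an error or disclosure, "a new randomization sequence will be generated starting from the problematic serial number" (section 2.4).
- **Analysis.** Section 2.13 names one-way ANOVA with multiple comparisons and Student's t test, with Tamhane T2 as the alternative. None of these has a hospital term.

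The article does not say whether the list is fixed at 30 per arm, whether each hospital has its own list, or how many patients each hospital will enrol.

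**The concern.** Complete randomisation ordinarily means that each patient is allocated independently. Arm sizes then vary by chance, and the planned margin of 30 − 26 = 4 patients per arm, meant for withdrawals, can be used up before anyone withdraws. An equal-numbers list avoids this only if every envelope is used in order. Envelopes tied to screening numbers do not guarantee that.

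Balance by hospital matters because patients and operators are unblinded (section 2.5), the primary outcome is self-reported pain (section 2.11.1), routine drug treatment continues in every group (section 2.10), and recruitment mixes inpatients and outpatients (section 2.3). If outcomes differ between hospitals, arms spread unevenly over hospitals add noise that neither the stated allocation nor the stated analysis removes.

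**Working it through.** **1. The plan's own figure.** Section 2.12 gives DAS28 values of 4.17 (SD 0.94) and 4.86 (SD 1.40), so the difference is 0.69 and the root-mean-square SD is √((0.94² + 1.40²)/2) = 1.192. Two-sided 5% and 90% power need n = 2(1.960 + 1.282)² × 1.192²/0.69² ≈ 63 per group. The stated 26 does not reproduce; that is a separate matter, and 26 is used here only as the plan's own threshold. The step from 26 to 30 fits 26 × 1.15 = 29.9 (26/0.85 = 30.6 would give 31).

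**2. Literal reading: 90 independent allocations to three arms.**
- P(30/30/30) = 90!/(30!³ × 3⁹⁰) = 0.0091, or 0.9%.
- SD of one arm's size = √(90 × 1/3 × 2/3) = 4.5.
- From 1,000,000 multinomial draws: some arm below 26 in 46%; the gap between largest and smallest arm has median 9 (5th to 95th percentile 2 to 18).

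**3. Alternative reading: an equal-numbers list keyed to screening numbers.** With no unused envelopes, a list of 90 gives exactly 30/30/30. Otherwise the 90 randomised patients are a random subset of a longer balanced list (multivariate hypergeometric). The article gives no screen-failure rate, so these are assumptions:

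| Assumed failures | List length | P(30/30/30) | P(some arm below 26) |
|---|---|---|---|
| 10% | 99 | 9% | 0.2% |
| 20% | 114 | 4% | 5% |
| 30% | 129 | 3% | 10% |
| 40% | 150 | 2% | 17% |

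**4. Cost of unequal arms.** Two-sided power for the DAS28 difference is Φ(0.69/(1.192 × √(1/n₁ + 1/n₂)) − 1.960). It is 61.1% at 30 v 30 and 59.3% at 24 v 36, a loss of 1.8 points.

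**5. Balance within hospital.** Hospital sizes are not given, so two splits are assumed. The measure is the largest minus the smallest arm in the worst hospital.

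| Assumed sizes | Method | Median | P(6 or more) |
|---|---|---|---|
| 23/23/22/22 | complete randomisation | 7 | 81% |
| 45/20/15/10 | complete randomisation | 7 | 77% |
| 23/23/22/22 | fixed 30/30/30 list, no strata | 6 | 60% |
| 45/20/15/10 | fixed 30/30/30 list, no strata | 6 | 50% |

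**6. Hospital-stratified blocks, same splits.** In blocks of 3 the within-hospital difference is at most 1 and the smallest arm overall was 28 to 29. In blocks of 6 it is at most 2 and the smallest arm overall was 26. Exactly 30/30/30 occurred in only 12% to 33% of simulated trials, because each hospital can end on an incomplete block.

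**The case against.** The strongest reply is that the phrase in section 2.2 may be loose. The same sentence fixes 90 patients and a 1:1:1 ratio, and section 2.12 gives 30 per group, which suits a list fixed at 30 per arm. This stands: the 0.9% and 46% belong to the literal reading only, and a reader should not infer that the trial is bound to miss 30/30/30.

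Second, an article may leave blocks, strata and model covariates to the full protocol or analysis plan. Silence alone would be no finding. But the randomised table, the screening-number labels and the one-way analysis are affirmative statements, and as stated they do not secure the design.

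Third, section 2.4 also calls the envelopes sequentially numbered, and no section says when a screening number is issued or how unused envelopes are handled. So the loss of allocations follows from the labelling as described but is not certain, and it is minor if few patients fail screening. Nor does the labelling show that concealment fails: the envelopes are opaque and sealed, an independent custodian keeps them, and they are opened after eligibility and consent.

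Fourth, a reader might infer that hospital imbalance biases the comparison. It does not do so systematically. Unstratified randomisation is valid, the imbalance arises by chance, and sections 2.10 and 2.15 provide for operator training. What remains is lost precision and a result that is harder to interpret if hospitals differ.

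**Conclusion.** The point holds in a limited form: the procedure as written secures neither 30 per arm nor balance within hospital. Arm size is the lesser matter. How often an arm falls below 26 depends on the reading, from 46% under independent allocation to 0.2% to 17% under a balanced list with 10% to 40% assumed screen failures, and the power cost is about 2 points even at 24 v 36.

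Hospital balance is the greater matter. A difference of 6 or more in at least one hospital is likely under complete randomisation (about 77% to 81%), and still occurs in 50% to 60% of trials with a fixed list that is not stratified. These figures rest on the two assumed hospital splits. Whether the imbalance affects the results depends on how far outcomes differ between hospitals, which the article does not show. Restarting the sequence after an error adds to the uncertainty, since nothing stated restores balance with patients already allocated.

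**What to change.** 1. Generate the list in permuted blocks stratified by hospital. Vary the block sizes at random, conceal them from the sites, and do not limit them to very small blocks: operators know the allocations, and the practitioner who checks eligibility opens the envelope.
2. Replace the screening number on the envelope with a hospital-specific randomisation number, issued in strict order only once eligibility and consent are recorded.
3. Include hospital as a factor in the outcome model.
4. Describe the target as approximately 30 per arm.

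**Cost:** a new list and relabelled envelopes, and no extra patients. Hospital in the model uses 4 − 1 = 3 degrees of freedom. Blocking brings some predictability; larger blocks reduce it but loosen the balance, since an incomplete block of size b can leave a difference of up to b/3 in a hospital.

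If the full protocol already works this way, only sections 2.2, 2.4 and 2.13 of the article need correcting to match.

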**Figure 1. F1:**
[figure not shown]
Study flowchart. Serum indicators include ESR, CRP, RF, IL-1, IL-6, TNF-, IL-18, MMP-3. ESR = erythrocyte sedimentation rate, CRP = serum C-reactive protein, RA = rheumatoid arthritis.

### 2.3. Patients recruitment

There will be 3 prime strategies to recruit RA patients. The first strategy is to recruit participants from the outpatient and inpatient. Second, printed recruitment posters will be distributed in public clinics and nearby communities to enroll potential eligible study subjects. Third, we will post advertisements, through the Internet, social software, and so on, to briefly introduce our study, so as to attract possible patients who are willing to participate. There are two researchers concerning recruitment and registration of participants who meet the inclusion criteria.

### 2.4. Randomization and allocation concealment

Eligible patients will be randomly assigned to 3 groups in a 1:1:1 ratio. The computer-generated random number list will be concealed in sequentially numbered, opaque, and sealed envelopes which kept by an independent custodian to ensure allocation concealment. The patients’ screening sequence numbers will be printed on the outside while the group names will be printed inside the envelope. The practitioner will firstly verify each patient meet the eligibility criteria and sign the written informed consent form, and then open the sealed envelope which containing an allocation sequence number for each patient. If any error or disclosure regarding randomization occurs, a new randomization sequence will be generated starting from the problematic serial number and applied to subsequent patients from then on.

### 2.5. Blinding

Taking into account that the significant difference of treatment and the specificity of moxibustion, patients will understand their group allocation, so will the operators, meaning that double blinding the study is unfeasible. Consequently, we will strictly carry out random allocation in order to ensure the integrity of this research, meanwhile, the efficacy assessors and outcome statisticians should be blinded to avoid the bias resulting from subjective impression.

### 2.6. Inclusion criteria

Patients meeting all of the following criteria will be enrolled in the study:

Patients meeting the diagnostic criteria for RA according to the 2010 criteria of the American College of Rheumatology (ACR)/European League Against Rheumatism (EULAR) Collaborative Initiative,^[14]^ which means classification as “Diagnosis of RA” is based on the presence of synovitis in at least 1 joint, and the total score of 6 or higher according to the individual scores in 4 fields: number and location of affected joints (score range 0–5), serological abnormality (score range 0–3), synovitis duration (score range 0–1), acute phase related reactants (score range 0–1).Chief signs and symptoms are joint swelling, tenderness, and stiffness.Female or male aged from 18 to 65.Voluntarily participating in this study with a written informed consent form signed by the participants themselves.Participants can understand the scales, that is, which are used to measure trial outcomes.

### 2.7. Exclusion criteria

Subjects will be excluded if they meet one of the following criteria:

Overlap other rheumatic diseases such as systemic lupus erythematosus, Sjogren syndrome, severe knee osteoarthritis, etc.Severe extra articular manifestations, such as persistent high fever, interstitial pneumonia, renal amyloidosis, constrictive pericarditis, central nervous system vasculitis, which need to be treated with glucocorticoid.At present, patients who are participating in or have participated in other clinical studies on the treatment of RA within 1 month before this study; acupuncture or moxibustion treatment for the disease during the past 1 month.Severe primary disease or infectious diseases including kidney, heart or liver disease, hematopoietic system, endocrine system disease, or pregnancy or breastfeeding.A severe psychological disorder or psychiatric condition associated with dementia and severe neurosis and inability to communicate or take care of oneself.With active gastrointestinal disease or peptic ulcer within 30 days before the study.Any other condition that the investigator consider as likely to make the patient incapable to complete, comply, or unsuitable for the clinical trial.

### 2.8. Withdrawal or dropout criteria

The participant has an AE related to the research.Those who can’t be judged the curative effect, or whose data are incomplete to affect the measurement of curative effect or safety.Although they met the inclusion criteria and were included, they did not receive any treatment related to this trial.At the participant’s own request.

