### 2.10. Interventions

Moxibustion staff members who have more than one year experience in Du moxibustion will be called for this trial and retrained for standard operation before the trial. The moxibustion acupoints are identified in accordance with the method of acupoint location issued by the World Health Organization (WHO).^[15]^ Du moxibustion treatment will be carried out from DU14 (Dazhui) to DU1 (Changqiang). The patient will be in prone position with bare back and be covered with a strip of gauze to prevent scalding. Large and long moxibustion box (60 cm long) will be placed on the back to cover the acupoints. Place the moxa velvet evenly in the moxibustion box (about 3 cm in height and 2 cm in width), ignite the moxa velvet from the top, and let it burn from top to bottom. Remove the ash of moxa after it is burned out (Fig. 2). The total time of moxibustion each time is about 30 minutes. After the treatment, the moxibustion box will be removed, with the degree of local skin flush and no blister. Moxibustion treatment will be conducted 3 times a week for 6 weeks. The patients will be followed up for 3 months. Patients in group A and B will be treated with Du moxibustion at 7 to 9 am and 5 to 7 pm, respectively. The group C will not receive any adjunctive treatment during the trial period, and then accept moxibustion treatment after the investigation. During the trial, the patients in each group will maintain the routine drug treatment.

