### 2.13. Statistical analysis

To eliminate artificial error, two statisticians blinded to the whole trail process will independently perform the statistical analysis by using SPSS statistics software (version 21) and Halberg cosiner software.

Baseline data including age, sex, disease duration, SF-MPQ score, joints morning stiffness score, joints swelling index, joints tenderness index, DAS28 score and laboratory indicators results before interventions will be analyzed with different approaches. All the data will be presented as mean ± standard deviation (SD). If the continuous variables can meet a normal distribution and homoscedasticity, One way analysis of variance (ANOVA) with multiple comparisons will be applied to identify differences more than two groups, while Student *t* test for pairwise comparison. Otherwise, we will use Tamhane T2 method instead. Halberg cosiner software will be used to analysis the circadian rhythm. *P* value is under .05 will be taken as statistically significant for each outcome. We will select the intention-to-treat principle to perform this statistical analysis. Thus, missing data will be imputed by using the multiple imputation method.

We will use two different methods: intention-to treat and per-protocol, for sensitivity analysis.

Halberg cosiner software will be utilized to analysis the circadian rhythm. For using the program, we will create time series per file (with the time tag, mean and SD). Then, the program will fit the cosine curve and polar coordinates and judge whether the parameters can show a circadian rhythm. By the formula of cosine curve, the results will be given, such as mesor, amplitude, acrophase. The results were considered significant when the *P* value <.05.

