### 2.14. Safety and AEs

The group A and B may encounter AEs including allergic reactions, skin burn, general fatigue, stomach upsets, headaches, bleeding tendency, dizziness, fainting and constipation.^[17]^ If the above condition occurs, the Du moxibustion treatment should be stopped immediately. These AEs will be subcategorized by severity: mild, moderate, and severe AEs (mild AEs = AEs are transient and tolerable; moderate AEs = AEs will cause discomfort and interfere with the subject’s normal life; severe AEs = serious impact on the participants’ physical health and even lead to the risk of life). The record form will be filled if AEs occur during the treatment period including the time, duration, performance, measures to be taken, and the outcome.

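### Section 2.8 makes adverse events, incomplete data and non-receipt of treatment grounds for withdrawal without separating end of treatment from end of follow-up, and is not reconciled with the intention-to-treat analysis

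*Protocol article*

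**What the plan says.** Section 2.8 of the protocol article lists the withdrawal or dropout criteria. Besides the participant's own request, there are three:

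- "The participant has an AE related to the research";
- an effect that cannot be judged, or patients "whose data are incomplete to affect the measurement of curative effect or safety";
- "Although they met the inclusion criteria and were included, they did not receive any treatment related to this trial".

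Section 2.13 says: "We will select the intention-to-treat principle to perform this statistical analysis". It adds that missing data will be handled by multiple imputation, and then: "We will use two different methods: intention-to treat and per-protocol, for sensitivity analysis".

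Three other sections bear on the same patients. Section 2.9 has all participants followed up three months after treatment for effect and safety, and Table 1 schedules outcomes at Week 3, Week 6 and Month 3. Section 2.14 says "The group A and B may encounter AEs including allergic reactions, skin burn, general fatigue", goes on to further symptoms, and responds to such an event by stopping the moxibustion. On the waiting list, section 2.10 says: "The group C will not receive any adjunctive treatment during the trial period". Section 2.12 permits at most 15% withdrawal, with 30 recruited per group.

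**The concern.** Under intention-to-treat, what happens to a patient after randomisation does not decide whether that patient is analysed, and outcomes should be collected whether or not treatment continues. Section 2.8 makes three post-randomisation events grounds for withdrawal or dropout and does not say what the patient withdraws from: the moxibustion, the assessments or the analysis.

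If site staff take it to mean that assessments end, outcomes are lost for reasons connected with treatment. Two of the three criteria fall mainly on the moxibustion groups, so the loss would not be balanced against the waiting list. It could also differ between groups A and B if adverse events differ by time of day, and that comparison is the timing question the trial sets out to answer. Imputation would then lean on patients who tolerated moxibustion to stand in for those who did not. Patients know their allocation and the primary outcome is self-reported pain, so the design has little margin for a further difference between arms.

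**Working it through.** This is mainly a check of text against text.

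**Adverse event.** Section 2.8 sets no severity threshold, and section 2.14 counts transient, tolerable events as mild adverse events. A minor related event therefore meets the criterion. Section 2.14 responds by stopping moxibustion and says nothing of leaving the trial, while section 2.9 follows up everyone. The three sections do not settle whether this patient is still assessed.

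**Incomplete data.** Section 2.8 makes this a ground for dropout. Section 2.13 imputes missing data, which presupposes that patients with incomplete data stay in. The article does not say which provision governs.

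**No trial treatment received.** A randomised but untreated patient is one whom intention-to-treat is meant to keep. Group C receives no moxibustion during the trial, so the criterion can sensibly apply only to groups A and B. It is then specific to those arms.

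**Sensitivity analysis.** Section 2.13 makes intention-to-treat the main principle and then lists it again for sensitivity analysis. It cannot be a sensitivity analysis of itself; only per-protocol adds anything.

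**What the figures can show.** Section 2.12 gives a minimum of 26 per group. 26 × 1.15 = 29.9, which rounds to the planned 30. The 15% is thus an allowance for numbers lost and says nothing about who is lost. At the limit it is 30 × 0.15 = 4.5 patients per arm, from all causes.

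Let f be the fraction of an arm without outcomes, and D how much worse, in SD units, these patients would have scored than the rest. If they are left out, the arm mean looks better by f × D. The bias in a comparison with group C is the difference:

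bias = f(A) × D(A) − f(C) × D(C)

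The documents give neither f by arm nor D. Taking f between 0 and 0.15 and, as an assumption, D between 0 and 1:

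- loss in group A only, D = 0.5: 0.15 × 0.5 = 0.075 SD in favour of moxibustion;
- loss in group A only, D = 1: 0.15 × 1 = 0.15 SD in favour of moxibustion;
- the same f and D in both arms: 0;
- loss in group C only, D = 1: 0.15 SD against moxibustion.

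As a second illustration, also assumed: dropping the worst 1, 2 or 4 of 30 patients shifts an arm mean by 0.07, 0.13 or 0.24 SD. If removal correlates only 0.3 to 0.5 with outcome, the shift is about 0.02 to 0.12 SD. Both illustrations treat lost patients as left out of the analysis; imputation using baseline or Week 3 data would usually shrink them.

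**The case against.** The strongest reply is that section 2.8 merely says who counts as a dropout. Nowhere does the article say that these patients leave the analysis set. Section 2.13 can be read as keeping them in their allocated arm with imputed values and leaving them out of per-protocol only; section 2.9 follows everyone, section 2.14 stops only treatment, and section 2.15 asks for the cause of drop-out to be recorded. This stands against calling the text a flat contradiction, which a reader might infer. It does not remove the problem: imputation does not restore a visit that was never held, and nothing in section 2.8 tells site staff to hold it.

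It is also fair that selective loss is not confined to groups A and B. Section 2.14 says these groups may have the listed events, not that only they can. Group C undergoes the same repeated blood sampling, which could cause a related event, and the incomplete-data and own-request criteria apply to every arm. Mainly is therefore the right word, not only.

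A reader might also take "they did not receive any treatment related to this trial" to make the whole waiting list dropouts. That is strained: group C is a planned arm with its own assessments, and no moxibustion is its allocated condition.

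Finally, the absence of a sensitivity analysis for data missing not at random is no defect here. Such detail is commonly left to a statistical analysis plan, and none is shown.

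**Conclusion.** The concern holds as a rule badly fixed in the text. Section 2.8 does not separate the end of treatment from the end of follow-up and is not reconciled with sections 2.9, 2.13 and 2.14. The clash is clearest for incomplete data, against imputation, and for non-receipt of treatment, against intention-to-treat. For adverse events it depends on whether withdrawal is taken to end assessment, which the article leaves open.

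If assessments end or patients are dropped on these grounds, missingness will differ by arm and may relate to outcome. Neither the size nor the direction of the bias can be derived from the documents. A reader might infer that moxibustion is favoured by 0.15 SD, about 26% of the planning effect (0.69/1.192 = 0.58 SD; 0.15/0.58 = 26%). The documents do not support that figure. It assigns the whole permitted loss to selective loss in a moxibustion arm and none to the comparator. It assumes a 1 SD deficit with no source and ignores imputation. Its denominator is a DAS28 effect, whereas the primary outcome is the SF-MPQ.

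**What to change.** Reconcile sections 2.8, 2.9, 2.13 and 2.14:

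1. In 2.8, distinguish stopping moxibustion from leaving the study. Patients who have an adverse event, or who stop or never start moxibustion, keep the scheduled Week 3, Week 6 and Month 3 assessments unless they withdraw consent.
2. Remove incomplete data and non-receipt of treatment from the withdrawal criteria. Non-receipt may be used only to define the per-protocol set, for groups A and B.
3. In 2.13, state that all randomised patients are analysed in their allocated arm, with intention-to-treat as the primary analysis and per-protocol as the sensitivity analysis.

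The treatment-stopping rule in 2.14 is not changed. The cost is protocol wording and a briefing of site staff, since the visits are already in Table 1. The change should be in place before patients reach these visits, because outcomes not collected cannot be recovered at the analysis stage.
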